##### 4.4.7.2 *Concomitant therapy*

Concomitant use of tocilizumab, canakinumab, TNF inhibitors and JAK inhibitors is not allowed.

Antimicrobial therapy and prophylaxis are not limited.

Analgesic treatment, transfusion of blood products, electrolyte and glucose infusions, i.v. parenteral nutrition, inotropic support, antibiotics, anti-fungal and anti-viral treatments, ultrafiltration or hemodialysis, as well as general supportive care are permitted.

Other therapy considered necessary for the patient's welfare may be given at the discretion of the Investigator.

All relevant concomitant therapy, as defined by the Investigator, will be recorded in the CRF.

#### 4.4.8 Treatment compliance

The IMP administrations will be recorded in the CRF.

Product accountability records will be kept. The pharmacy and Investigator must maintain accurate records demonstrating date and amount of study drug(s) received, to whom and by whom administered or dispensed (patient-by-patient accounting).

#### 4.4.9 Rescue Medication

All patients must have access to rescue treatment with independent of the assigned arm.

If a patient withdraws due to worsening of disease, patient should be treated as a non-responder.

In the case of a patients starts to worsening independent of the assigned arm, , the patient will be able to receive treatments that are protocolized at their hospital. The patient could be treated with pulses of steroids, intravenous immunoglobulins, betainterferon , immunosuppressants agents such as cyclosporin, tacrolimus and other biologic agents such as baricitinib , tocilizumab, sarilumab and ruxolitinib. If the patient need therapy with biological drugs they should be removed from the study.

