#### 4.3.3 Withdrawal of patients from treatment or study

##### 4.3.3.1 *Withdrawal from treatment*

A patient should be withdrawn from the study treatment if, in the opinion of the Investigator, it is medically necessary, or if it is the wish of the patient.

When a patient is withdrawn, the date of last IMP (investigational medicinal products) administration and the date and reason for treatment withdrawal should be clearly described in the relevant sections of the CRF. If a patient is removed from treatment because of an AE, the reason for treatment withdrawal should always be stated as 'adverse event' irrespective of whether this was the investigator's or the patient's decision.

If a patient withdraws due to worsening of disease, patient should be treated as a non-responder. In these case, the patient will be able to receive treatments that are protocolized at their hospital. The patient could be treated with pulses of steroids, intravenous immunoglobulins, betainterferon and other biologic or immunosuppressants agents such as cyclosporin, tacrolimus, baricitinib, tocilizumab, sarilumab, ruxolitinib...

The patient will continue to participate in the study without taking study treatment.

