##### 4.3.3.2 *Withdrawal from study*

Whenever possible and irrespective of the reason for withdrawal, the patient should be examined as soon as possible. Relevant samples should be obtained, and all relevant assessments should be completed. The CRF should be completed as far as possible. Date and reason for the study withdrawal should be clearly described in the CRF.

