#### 4.3.4 Replacement of withdrawn patients

Patients withdrawn from the study will not be replaced.

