#### 4.4.6 Blinding and unblinding

This is an open study with no level of blinding.

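### Section 4.4.9 removes patients who need a biologic from the study, while section 4.3.3.1 keeps the same patients in follow-up off treatment

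*Protocol*

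**What the plan says.** Two sections of the Protocol cover the patient who worsens and is given a biologic or similar agent.

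- **Section 4.3.3.1 (Withdrawal from treatment).** A patient withdrawn for worsening may receive "other biologic or immunosuppressants agents such as cyclosporin, tacrolimus, baricitinib, tocilizumab, sarilumab, ruxolitinib". The section ends: "The patient will continue to participate in the study without taking study treatment".
- **Section 4.4.9 (Rescue Medication).** Worsening patients in either arm may receive hospital-protocol therapy, and baricitinib, tocilizumab, sarilumab and ruxolitinib are again named. The section ends: "If the patient need therapy with biological drugs they should be removed from the study".

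Both sections carry the same outcome rule: "If a patient withdraws due to worsening of disease, patient should be treated as a non-responder".

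Leaving the study is a separate category, under section 4.3.3.2. There the site examines the patient and completes the CRF as far as possible: "Relevant samples should be obtained, and all relevant assessments should be completed". Nothing in that section asks for status at Day 15 or Day 28. Section 4.3.4 adds: "Patients withdrawn from the study will not be replaced". Section 4.4.6 states: "This is an open study with no level of blinding".

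**The concern.** The protocol distinguishes stopping treatment from leaving the study, so the two sections give different instructions for one patient, and different sites may follow different ones.

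If sites follow 4.4.9 literally, follow-up stops because the patient is deteriorating. Such patients still belong to the efficacy set if they were treated (section 6.2), and missing data are not to be filled in (section 6.3.8). Time to ventilation (6.3.3.2), ventilation at Day 28 (6.3.4.1) and mortality (6.3.4.2 and 6.3.4.3) would then be censored or missing for reasons tied to the outcome. Open-label rescue may also differ between arms. A statistical analysis plan cannot recover outcomes that sites were told to stop collecting.

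**Working it through.** **Step 1. Is it the same patient?** Both sections start from worsening disease, both allow hospital-protocol therapy, and both name the same four agents. 4.3.3.1 keeps the patient in the study; 4.4.9 takes the patient out. The conflict is in current text and needs no figure to establish it.

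**Step 2. What does literal removal lose?**

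| Outcome | Where it is collected | After removal from the study |
|---|---|---|
| Date of ventilation | Visits 1 to 4 (4.5.3.1) | Not requested |
| Survival | Follow-up visits (Table 3, 4.5.3.7) | Not requested |
| Death as a fatal SAE | Up to the end of study visit (4.5.4.3) | Unclear: the protocol does not say which visit this is for a removed patient |
| Non-responder status | 4.3.3.1 and 4.4.9 | Available, but 3.1.1 and 6.3.3.1 define the endpoint by ventilation alone and do not mention it |

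**Step 3. How large could the effect be on ventilation?** The protocol gives no rescue rates, so the loss shares below are assumptions.

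Inputs: 90 patients per arm and success rates of 88% and 92% (section 6.1). These Day-15 planning rates stand in for Day 28.

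- Planned events: 0.12 × 90 = 10.8 control and 0.08 × 90 = 7.2 anakinra, 18 in all.
- Hazard ratio with full follow-up: ln(0.92) / ln(0.88) = 0.652.
- Let sC and sA be the shares of would-be ventilated patients who get a biologic first and are lost. The observed hazard ratio is then about 0.652 × (1 − sA) / (1 − sC).
- Section 6.3.3.2 plans a 90% interval: HR × exp(±1.645 × SE), with SE = √(1/dC + 1/dA) and dC, dA the observed events.

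Equal losses:

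| Share lost, both arms | Events (dC + dA) | SE | HR | 90% interval |
|---|---|---|---|---|
| 0% | 10.8 + 7.2 = 18 | 0.481 | 0.65 | 0.30–1.44 |
| 25% | 8.1 + 5.4 = 13.5 | 0.556 | 0.65 | 0.26–1.63 |
| 50% | 5.4 + 3.6 = 9 | 0.680 | 0.65 | 0.21–2.00 |

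Unequal losses:

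- 50% control, 25% anakinra: 0.652 × 0.75 / 0.50 = 0.978.
- 25% control, 50% anakinra: 0.652 × 0.50 / 0.75 = 0.435.

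A large Cox simulation (exponential times, 1,000,000 per arm, removal 1 to 3 days before ventilation) gives 0.657, 0.653, 0.977 and 0.436 for the four loss scenarios in the order above. Also removing an equal number of never-ventilated patients gives 0.641, 0.642, 0.951 and 0.438.

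Day-28 risk among patients with data, against a planned difference of 12.0% − 8.0% = 4.0 points:

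| Lost, control / anakinra | Control | Anakinra | Difference (points) |
|---|---|---|---|
| 25% / 25% | 8.1/87.3 = 9.3% | 5.4/88.2 = 6.1% | 3.2 |
| 50% / 50% | 5.4/84.6 = 6.4% | 3.6/86.4 = 4.2% | 2.2 |
| 50% / 25% | 6.4% | 6.1% | 0.3 |
| 25% / 50% | 9.3% | 4.2% | 5.1 |

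**Step 4. What if the non-responder rule is not applied to the primary endpoint?** Assume 11 control and 7 anakinra failures among patients not rescued, plus 10 and 5 rescued with a biologic.

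- Rescued patients counted as failures: 21/90 = 23.3% against 12/90 = 13.3%, p = 0.083 (uncorrected chi-square).
- Rescued patients dropped: 11/80 = 13.8% against 7/85 = 8.2%, p = 0.256.

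These counts are assumed too. They show only that the choice can matter.

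**The case against.** **The sentence may have meant study treatment only.** Section 4.4.7.2 says: "Concomitant use of tocilizumab, canakinumab, TNF inhibitors and JAK inhibitors is not allowed". On that view, a patient who needs such a drug simply stops anakinra. This is plausible and may be the intent. But the words say study, and the protocol has its own section for leaving the study, so a site acting on the literal text would not be misreading it.

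**The primary endpoint is largely protected.** The non-responder rule stands in both sections, so a patient withdrawn for worsening can be classified under either reading, and mapping the rule to failure could be left to the analysis plan. This largely stands. The primary endpoint is exposed only if the rule is not applied as failure.

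**The affected endpoints are secondary, and section 6.3.1 calls them descriptive.** This lowers the stakes but does not remove them. Sections 6.3.3.2, 6.3.4.1 and 6.3.4.2 still test and estimate these outcomes, and selectively missing data mislead a descriptive summary as well.

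**Removal is not withdrawal of consent.** Hospital records remain the source, and the CRF is to be completed as far as possible. Some outcomes could therefore be recovered, but the protocol does not require it.

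**The size is assumed and modest.**

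- Equal shares do not move the hazard ratio. They lose 4.5 or 9 of 180 patients (2.5% or 5%), below the planned 10% loss. That allowance covers numbers, though, not informative loss.
- Both shifted ratios lie inside the full-follow-up interval of 0.30–1.44.
- If equal numbers of never-ventilated patients are removed too, the equal-share differences become about 3.3 and 2.5 points instead of 3.2 and 2.2.

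All of this is fair. The figures illustrate; they do not predict.

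**Mortality has no rate behind it.** This is also correct. No mortality rate, rescue rate or rate of missed deaths is given, so a mortality effect can be described but not sized.

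**Conclusion.** The concern holds, and the point should be fixed. The two instructions conflict in current text, and literal compliance with 4.4.9 ends follow-up in worsening patients without asking for their ventilation or survival status.

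Size and direction are unknown because no rescue rates are given. If losses are equal between arms, the cost is mainly precision and a smaller absolute difference. Bias in the hazard ratio needs unequal losses, which an open-label design does not prevent; the assumed 25% against 50% splits multiply it by 1.5 or 0.67. All of this assumes that removed patients are lost before ventilation and that planned Day-15 rates serve for Day 28.

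Mortality could be distorted in the same way, to the extent that deaths after removal are not captured as fatal SAEs.

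**What to change.** 1. **Section 4.4.9:** replace removal from the study with withdrawal from study treatment and continued follow-up to Day 28 for ventilation and survival, in both arms, matching 4.3.3.1.
2. **Day-28 contact:** record ventilation as well as survival, because 4.5.3.1 lists ventilation only for Visits 1 to 4.
3. **Sections 3.1.1 and 6.3.3.1:** add one sentence stating how the non-responder rule enters the endpoint, applied identically in both arms. Whether it belongs in the primary or a sensitivity analysis is the sponsor's choice.

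Reporting biologic rescue by arm would help readers, but it is a preference and not a correction.

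The cost is a reworded sentence, a linking sentence, an added Day-28 item and slight extra follow-up, which section 4.5.1.6 already allows by telephone. The trade-off is that outcomes after a biologic will include the effect of that rescue.

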### 4.5 Efficacy and safety assessments

#### 4.5.1 Study schedule

##### 4.5.1.1 Schedule of events

Measurements will be done during screening (before Day 1), at Day 1, Day 4, Day 7, and Day 15 and Day 28.

Table 3: Clinical and laboratory parameters to be collected

| ASSESSMENT             | SCREENING        | TREATMENT PERIOD |         |         |                  | Follow-up         |
|------------------------|------------------|------------------|---------|---------|------------------|-------------------|
|                        | Prior to Visit 1 | Visit 1          | Visit 2 | Visit 3 | Visit 4          | Visit 5/TC        |
|                        |                  | Day 1 (Baseline) | Day 4   | Day 7   | Day 15 (± 2 day) | Day 28 (± 2 days) |
| Informed consent       | X                |                  |         |         |                  |                   |
| Eligibility criteria   | X                | X                |         |         |                  |                   |
| Patient information    | X                |                  |         |         |                  |                   |
| Physical examination   | X                |                  |         |         |                  |                   |
| Vital signs assessment | X                | X                | X       | X       | X                |                   |
| EKG assessment         | X                |                  |         |         | X                |                   |
| Chest X-Ray            | X                |                  |         |         | X                |                   |

|                                                |   |     |   |   |   |   |
|------------------------------------------------|---|-----|---|---|---|---|
| Laboratory assessments (local)                 | X | X   | X | X | X |   |
| Urine pregnancy test                           | X |     |   |   | X |   |
| Randomization                                  |   | X   |   |   |   |   |
| IMP administration                             |   | X X |   |   |   |   |
| Concomitant medication incl background therapy |   | X   | X | X | X |   |
| Pulmonary function                             |   | X   | X | X | X |   |
| PaO 2 /FiO 2             | X |     |   |   | X |   |
| Resting SpO 2 (3 times per day)     |   | X   | X | X | X |   |
| Oxygen supplementation                         |   | X   | X | X | X | X |
| MEWS score                                     |   | X   |   |   | X |   |
| Survival                                       |   |     |   |   |   | X |
| Time to hospital discharge                     |   |     |   |   |   | X |
| Adverse events                                 |   | X   | X | X | X |   |
| Biomarkers                                     |   | X   | X | X | X |   |

#### 4.5.1.2 Screening

Screening will occur prior to Visit 1 (Baseline). The aim of the screening is to collect necessary data to confirm the patient's eligibility and can be ongoing up the randomization of the patient at Visit 1. A signed informed consent form must be obtained from the patient prior to any study-related activities. However, laboratory results already available in medical records at the time of informed consent can be used to confirm eligibility, if collected prior to Visit 1. Please refer to Table 3 for the clinical and laboratory parameters to be collected during screening.

Patients who do not meet the criteria for participation in this study (screening failure) may not be rescreened.

#### 4.5.1.3 Visit 1, Baseline (Day 1)

Once all inclusion and exclusion criteria have been reviewed and recorded, and the patient has been found eligible, the patient will be randomized into one of the treatment groups and the first dose of study drug will be administered accordingly (see Section 4.4.1). Please refer to

Table 3 (see Section 4.5.1), for other clinical and laboratory parameters to be collected during the visit.

During the treatment period, clinical and laboratory assessments and procedures should preferably be performed before IMP administration.

#### *4.5.1.4 Visits 2 to 3 (Days 4 and 7)*

Please refer to Table 3 for the clinical and laboratory parameters to be collected during these visits. For study drug administration schedule, see Section 4.4.1.

Effort should be made to adhere to the schedule of assessment. However, a window of  $\pm 1$  day will be allowed for all assessments scheduled. This does not include IMP administration.

During the treatment period, clinical and laboratory assessments and procedures should preferably be performed before IMP administration.

#### *4.5.1.5 Visit 4 (Day 15)*

Please refer to Table 3 for the clinical and laboratory parameters to be collected during these visits. For study drug administration schedule, see Section 4.4.1.

Effort should be made to adhere to the schedule of assessment. However, a visit window of  $\pm 2$  day will be allowed for Day 15.

During the treatment period (Days 1 to 15), clinical and laboratory assessments and procedures should preferably be performed before IMP administration.

The primary endpoint will be evaluated at Day 15.

#### *4.5.1.6 Follow-up (Day 28)*

These visits can be conducted either as a follow-up telephone call or in-person visit, if the patients is still hospitalized. Please refer to Table 3 for the clinical parameters to be collected during the visits.

A window of  $\pm 5$  days will be allowed.

#### 4.5.2 Patient information and physical examination

##### *4.5.2.1 Demographics*

The patient's date of birth and gender will be collected at screening and recorded in the CRF.

##### *4.5.2.2 Medical and surgical history*

Details of the patient's relevant medical and surgical history as judged by the Investigator will be collected at screening and recorded in the CRF.

##### *4.5.2.3 Prior medication*

Details of the patient's relevant prior medication as judged by the Investigator will be collected at screening and recorded in the CRF.

##### *4.5.2.4 Physical examination*

A general physical examination will be performed at screening and recorded in the CRF. The assessment will be reported as "normal" or "abnormal". Any abnormalities should be specified and recorded as medical history.

Body weight and height will be recorded as a part of the physical examination.

#### 4.5.3 Efficacy assessments

##### *4.5.3.1 Pulmonary function (primary efficacy assessment)*

The date and time of the requirement for mechanical ventilation will be assessed at Visits 1 to 4, and recorded in the CRF.

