##### 3.1.2 Secondary endpoints supporting the primary objective

- Number of patients not requiring mechanical ventilation (day 28).
- Time to mechanical ventilation (days)
- Time to oxygen saturation normalization
- Stay in ICU and hospitalization (days)

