##### 3.2.1 Secondary endpoints supporting the secondary objective

- Total mortality rate (day 28)
- Mortality 48 hours, 7 days, in ICU and hospital
- Viral clearance / viral shedding
- Frequency and severity of AEs:
  - Treatment-emergent severe fatal and life-threatening serious adverse events (SAEs).
  - Adverse events leading to premature discontinuation of study treatment.
  - Anaphylactic/anaphylactoid reactions.

- 
- Anakinra treatment group: Severe neutropenia.
  - Treatment-emergent laboratory abnormalities.

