#### 6.3.4 Analysis related to secondary objective

##### *6.3.4.1 Mechanical ventilation at day 28.*

The percentage of patients requiring mechanical ventilation at 28 days after the start of treatment. The comparison of these proportions would be done by chi-square test, with significance level 0.05 and presentation in the form of absolute risk reduction, relative risk reduction and number needed to treat, with their respective 95% confidence intervals.

---

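### No ventilation assessment is scheduled after Day 15, so the Day-28 ventilation endpoint is not systematically supported; the Day-28 contact also has two conflicting windows

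*Protocol*

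**What the plan says.** - **Ventilation data.** Section 4.5.3.1 reads: "The date and time of the requirement for mechanical ventilation will be assessed at Visits 1 to 4, and recorded in the CRF". In Table 3 (section 4.5.1.1) the corresponding row, "Pulmonary function", is marked at Visits 1 to 4 and blank at Visit 5 (Day 28).
- **Day-28 contact.** Section 4.5.1.6 defines its content by reference: "Please refer to Table 3 for the clinical parameters to be collected during the visits". At Visit 5 the table marks only oxygen supplementation, survival and time to hospital discharge.
- **Day-28 endpoint.** Section 3.1.2 lists freedom from mechanical ventilation at Day 28 as a secondary endpoint. Section 6.3.4.1 analyses it as "The percentage of patients requiring mechanical ventilation at 28 days after the start of treatment" and adds: "The comparison of these proportions would be done by chi-square test, with significance level 0.05", with absolute and relative risk reduction, number needed to treat and 95% confidence intervals.
- **Window.** Table 3 gives Day 28 ±2 days. Section 4.5.1.6 gives ±5 ("days will be allowed"). Section 4.1 caps an individual patient's participation at 4 weeks. Section 4.5.3.7 places survival and discharge data at Visits 5 and 6, but Table 3 ends at Visit 5.
- **Virology.** Section 3.2.1 lists "Viral clearance / viral shedding" as a secondary endpoint. Neither Table 3 nor Table 4 contains a virological sample. The only one in the protocol is the positive smear required for inclusion.

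**The concern.** A planned comparison needs an outcome that somebody is told to collect. Two separate places in the protocol stop the ventilation item at Visit 4, so this does not look like a slip in one table cell. A later SAP cannot repair it, because it cannot analyse what the CRF never asked for.

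The Day-28 endpoint has a specific purpose. Anakinra stops by Day 15 at the latest, so only later data can show whether ventilation was prevented or merely postponed. If late ventilation goes unrecorded, a temporary effect would appear as a sustained one. The trial is open-label, so late cases retrieved ad hoc could also be sought differently in the two arms.

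The two windows matter because mortality and discharge depend on the same contact. If it takes place before Day 28, the patient's Day-28 status is unknown.

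**Working it through.** The protocol states no figure for this point, so there is none to reproduce. The check compares visit coverage with what the endpoints need, using day arithmetic.

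**1. Coverage of ventilation.**
- Last scheduled assessment: Visit 4, Day 15 ±2, so Day 13 to Day 17 (Table 3, section 4.5.1.5).
- Endpoint horizon: Day 28.
- Gap: 28 − 15 = 13 days, or 13/28 = 46% of calendar follow-up. With the window it is 28 − 17 = 11 to 28 − 13 = 15 days.

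**2. Other routes by which late ventilation might be recorded.**
- Oxygen supplementation at Visits 1 to 5 (section 4.5.3.4) takes date, time and amount. It is not defined to include mechanical ventilation, which has its own item.
- Fatal and life-threatening SAEs are reported up to the end-of-study visit (section 4.5.4.3). No rule says that each intubation must be reported this way or that its date feeds the endpoint.

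Both routes are incidental.

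**3. Possible number of missed events (illustration).** The protocol does not say how many ventilations start after Day 15. Let f be that share, assumed to be 5% to 20%. Let p be the total proportion ventilated, 12% to 15%, from section 6.1 (1 − 0.88, and the 15% seen in the hospital database). Missed events per arm of 90 = 90 × p × f:
- Low: 90 × 0.12 × 0.05 = 0.54
- High: 90 × 0.15 × 0.20 = 2.70

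For comparison, the difference assumed in section 6.1 is 90 × (0.92 − 0.88) = 3.6 patients per arm.

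**4. Prevented versus delayed (extreme case, for illustration).** Suppose the section 6.1 rates hold at Day 15: 90 × 0.12 = 10.8 ventilated on standard of care and 90 × 0.08 = 7.2 on anakinra. Suppose too that the 3.6 apparently spared patients are all ventilated between Day 16 and Day 28, with no other late events. The true Day-28 risk difference is then 0. Data from Visits 1 to 4 alone would still give 4 percentage points and a number needed to treat of 1/0.04 = 25.

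**5. The windows.**
- Table 3: 28 ± 2, so Day 26 to Day 30.
- Section 4.5.1.6: 28 ± 5, so Day 23 to Day 33.
- Earliest compliant contact: 5 days short of Day 28 (5/28 = 18%) under ±5, and 2 days short (2/28 = 7%) under ±2.
- Both upper limits, Day 30 and Day 33, exceed the 4-week cap in section 4.1.

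The effect depends on the analysis. In a crude Day-28 proportion, a survivor last contacted on Day 23 and counted as event-free can only push the rate down. In the Kaplan-Meier and Cox analysis that section 6.3.4.2 plans for mortality, the same patient is censored on Day 23, which loses information.

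**6. ICU stay.** Section 6.3.3.2 analyses time in ICU at the end of follow-up, but Table 3 has no item for ICU admission or discharge dates.

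**The case against.** The strongest defence is that the gap touches only a secondary endpoint. The primary endpoint is at Day 15 and Visits 1 to 4 cover it. Section 6.3.1 treats secondary endpoints descriptively and their p-values as exploratory, so no primary conclusion, sample size or error rate depends on Day-28 ventilation. That stands, and it limits the weight of the point.

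The 46% is calendar time, not events. Section 2.1 places deterioration around days 7 to 10 from symptom onset, and patients enter with severe pneumonia, so most ventilation probably starts early. That also stands. It is why step 3 gives a small count under a stated assumption.

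Three stronger readings are tempting but not supported:

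- **A reader might infer that the Day-28 endpoint has no data at all.** On a cumulative reading, which the primary endpoint's wording favours, events up to Day 15 count towards it, and some later events may surface through SAE reports or the oxygen item. What is missing is systematic capture after Day 15.
- **A reader might infer that early calls bias the mortality analysis downwards.** Section 6.3.4.2 plans a time-to-event analysis, in which early contact means censoring. Understatement follows only for a crude Day-28 proportion, which the mortality rate label in section 3.2.1 may invite.
- **A reader might infer that time to ventilation is wrongly cut off.** Sections 3.1.2 and 6.3.3.2 give it no Day-28 horizon, and censoring at the end of the treatment period is legitimate if stated.

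None of this removes the contradiction between the schedule and the Day-28 endpoint, or between the two windows.

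**Conclusion.** The point holds in limited form. Followed as written, the protocol does not systematically capture ventilation that starts in the last 13 days (11 to 15) of a 28-day endpoint. The Day-28 comparison could largely repeat the Day-15 one and could not tell prevention from delay. If 5% to 20% of ventilations occurred after Day 15, about 0.5 to 2.7 events per arm of 90 would be at risk of being missed. That share is an assumption; the documents give no figure.

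The ±2 and ±5 windows contradict each other, and both overrun the 4-week cap. The viral clearance endpoint has no scheduled sample after screening.

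This should be fixed, but it does not threaten the trial's main result: the Day-15 primary endpoint is unaffected.

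**What to change.** 1. **Visit 5 data.** Add mechanical ventilation since the last visit (yes/no, start and stop dates) and ICU admission and discharge dates, taken from the chart or the call already planned. Amend section 4.5.3.1 and Table 3 to match.
2. **One Day-28 window.** State it identically in Table 3 and section 4.5.1.6, with contact on or after Day 28 and events counted by date through Day 28.
3. **Consequential wording.** Align the 4-week maximum in section 4.1, which a contact after Day 28 would otherwise breach. Correct the reference to Visits 5 and 6 in section 4.5.3.7.
4. **Viral clearance.** Remove it as an endpoint, or state that it uses only results obtained in routine care.

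The cost is a few CRF lines at an existing contact and protocol wording. No visit, sample or patient is added, and the sample size does not change.
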